# Evaluating the effectiveness and cost‐effectiveness of integrating mass drug administration for helminth control with seasonal malaria chemoprevention in Ghanaian children: Protocol for a cluster randomised controlled trial

**DOI:** 10.1111/tmi.14062

**Published:** 2024-11-27

**Keywords:** African children, geohelminths, integration, malaria, schistosomiasis

## Abstract

**Objectives:**

To evaluate the effectiveness and cost‐effectiveness of integrating seasonal malaria chemoprevention (SMC) with mass drug administration for helminth control among school‐aged children living in communities where the burden of malaria and helminths is high in Ghana, West Africa.

**Methods:**

This cluster randomised controlled trial will enrol 1200 children aged 5–10 years. Eligible children randomised to intervention clusters will receive SMC drugs (sulphadoxine‐pyrimethamine plus amodiaquine) and anthelminthic drugs for soil‐transmitted helminths—(albendazole), and for schistosomiasis (praziquantel), while children randomised to control clusters will receive SMC drugs alone. Pre‐ and post‐intervention blood, urine and stool samples will be collected from children in both clusters. The effectiveness of the concomitant delivery will be determined by checking whether the combination of SMC and anthelminthic drugs prevents anaemia in the children randomised to the intervention clusters compared to the children in the control clusters. Cost analysis and cost‐effectiveness of this integrated delivery approach will be determined by estimating the incremental costs and effects of co‐administration of SMC drugs with mass drug administration of anthelminthic drugs compared to SMC alone, including cost savings due to cases of moderate and severe anaemia averted.

**Expected findings:**

The findings of this study will provide evidence to inform public health recommendations for an integrated control of malaria and helminths among children living in the poorest countries of the world.

## INTRODUCTION

The changing epidemiology of malaria has shifted the burden of malaria to children aged above 5 years in many high transmission areas in sub‐Saharan Africa (SSA), with increased recognition of the consequences of malaria in school‐age children, including the detrimental effects of anaemia. This development is further aggravated by the frequency of co‐infection of malaria and helminths in many endemic settings in SSA. The geographical and epidemiological overlaps of malaria and helminth infections create an opportunity for the development and implementation of an integrated control approach for malaria and helminths [1, 2, 3].

While modest progress in the control of schistosomiasis and soil‐transmitted helminths (STH) has been achieved through mass drug administration (MDA) of albendazole (ALB) and praziquantel (PZQ) and has informed improved strategies articulated in the neglected tropical diseases (NTD) roadmaps 2030 [4], the remarkable success of seasonal malaria chemoprevention (SMC) has led to the recent World Health Organisation (WHO) recommendation for its extension to other at‐risk age groups in highly seasonal malaria transmission settings outside the Sahel region [5]. This encouraging development supports the need to explore the possibility of integrating helminth control programme with other successful delivery platforms, such as SMC, especially in countries where SMC is given to older children. Additionally, in line with the strategies of the WHO roadmap to end the neglect on NTDs, achieve the Sustainable Development Goals (SDG) 3 and 4, and ensure universal health coverage, WHO has endorsed an integrated approach of joint delivery of interventions through a common platform, such as preventive chemotherapy, integrated monitoring, evaluation and reporting [6]. Driven by the WHO recommendation of promoting the global trend towards integrated, non‐disease‐specific approaches to controlling co‐endemic diseases such as malaria and helminths [6], we demonstrated in a randomised controlled trial the feasibility, safety and acceptability of integrating MDA for schistosomiasis and STH with SMC delivery to pre‐school and school‐age children living in a co‐endemic setting in Senegal [7, 8].

To maximise the impact of our findings, we will evaluate the effectiveness of the integrated SMC and MDA of anthelminthic drugs on the prevalence of anaemia and malaria‐helminth co‐infection in a larger paediatric population than was included in the pilot trial. This study will test the hypothesis that haemoglobin (Hb) concentration will be higher in the combined SMC‐MDA group than in the SMC alone group. Given that the analysis of the economic and financial costs of delivering the integrated model will be needed to inform resource allocations, allow comparison with alternative interventions, and inform deployment of the approach, if successful, we will also evaluate the costs and cost‐effectiveness of the integrated delivery model for SMC‐MDA among the study children. The analysis will also explore how costs vary with drug prices, organisation of the delivery of the integrated approach, and how cost‐effectiveness varies depending on the differences in the effectiveness and background prevalence of anaemia [9].

## METHODS

### Study design

This will be a cluster randomised, controlled, programme‐led pragmatic study to evaluate the effectiveness of co‐administration of SMC and MDA for schistosomiasis and STH in reducing anaemia due to malaria‐helminth co‐infections among school‐age (5–10 years old) children. The trial has been registered on Clinicaltrials.gov NCT06182176 and Pan‐African Clinical Trials PACTR202312489417172. The interventions for this study are the WHO‐approved drugs for preventive treatment of malaria (sulphadoxine‐pyrimethamine [SP] + amodiaquine [AQ] [SPAQ]) [10], and helminths (ALB and PZQ) [11]. These interventions will be delivered jointly by the Ghana Health Service‐led SMC and NTD control programmes, to the children enrolled in this study. The children will be enrolled at community levels and the communities will be assigned into two equal clusters, to receive either combined SMC and anthelminthic drugs or SMC drugs only. To minimise the potential for contamination and spill‐over effect, the study communities will be separated from each other by at least 5 km. To ensure objectivity in the reporting of adverse events among the children across the two clusters, vitamin A and zinc supplement will be given to children in the control clusters randomised to receive SMC drugs only. This approach will ensure that children in the intervention and control clusters receive three drugs. Vitamin A and zinc supplements have not been shown to affect the outcomes of this study [12, 13].

### Study population

This study will be conducted in communities within Pru East district, Bono East Region, within the forest‐savannah, transitional ecological zone in the middle belt of Ghana (Figure 1). The district experiences tropical continental or interior savannah type of climate which is a modified form of tropical continental or wet‐semi equatorial type. Major rains occur in September and October and minor rains in May and June; the annual rainfall is between 1400 mm and 1800 mm. There is a prolonged dry season between November and April. Relative humidity is 75%–80% in the wet season and 70%–72% in the dry season [14, 15, 16]. The hottest months are March and April. The main vectors for transmission of malaria are *Anopheles gambiae* and *Anopheles funestus* and malaria transmission is perennial, but peaks between April and October [17]. According to the 2022 Ghana Demographic and Health Survey, the prevalence of malaria among under‐five children in Bono East Region was 22.1% by rapid diagnostic kit test (RDT) and 12% by microscopy [18]. Similarly, the study area was reported to be endemic for schistosomiasis and STH [15].

**FIGURE 1 tmi14062-fig-0001:**
[figure not shown]
Map showing the study area in central Ghana. 
*Source*: Ghana Statistical Service, GIS. GIS, geometric information system.

### Sample size determination

We assumed that the mean Hb concentration in the SMC alone group will be 10.5 g/dL with a standard deviation of 1.5 g/dL [3]. Assuming an intra‐class correlation coefficient of 0.05, then 10 communities per cluster, a study of 60 children per community will have 80% power to detect an increase in mean Hb of 0.5 g/dL (to 11.0 g/dL) in the SMC plus anthelminthic group as statistically significant at 5% level. A minimum sample size of 1200 school‐age children (5–10 years) will be enrolled. This study will be implemented in three stages: pre‐intervention, intervention and post‐intervention. The pre‐intervention survey will be conducted to determine the prevalence of malaria‐helminth co‐infection in the study population.

#### Sampling for pre‐intervention stage

The Lot Quality Assurance sampling technique [19] will be used to recruit study participants in the pre‐intervention stage. For example, a total of 15 children, with a roughly even mix of boys and girls, ranging in ages from 5 to 10 years, will be randomly selected in each school within a selected community.

#### Sampling for the intervention stage of the trial

There will be two study arms in the intervention phase of this trial—intervention and control arms. Ten schools within Pru East communities will be randomised to the intervention arm and another 10 schools will be randomised to the control arm. As calculated above, a minimum of 60 children who satisfy all eligibility criteria will be enrolled sequentially in each of the 10 schools randomised into the intervention and control arm, respectively. To identify these children, we will undertake a census of all children aged 5–10 years in the communities selected for the intervention stage of the trial. Subsequently, we will use a sampling frame for random sampling from the census list to enrol the required number of children into each study arm. We will keep a reserve list of potentially eligible children in case of any refusals from the sampling list.

Data collection for the cost‐effectiveness analyses will involve semi‐structured interviews with key informants from the regional and district education and health offices, using purposive sampling to select health facility personnel, community health workers (CHWs) and school teachers involved in the delivery of SMC with or without MDA for helminths. Approximately 6–12 interviews are anticipated at the regional and district level, up to 10 with health facility personnel, 10–15 with CHWs and 10–20 with school teachers. Key informants will be chosen to reflect maximum expected variation across the study area, for example, a mix of urban and rural communities, distance from the district centre, etc. This flexible and purposive approach to sampling is a standard and important feature of economic evaluations.

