
##### Intervention stage

Given that the focus of this project is to evaluate the effectiveness of the integrated SMC‐MDA control programmes, the first day of starting the intervention stage (Day 0) will correspond to the day prior to the commencement of the first cycle of SMC in the study area. On Day 0, the communities will be randomised at community level into two clusters at 1:1 ratio to receive either combined SMC and anthelminthic drugs (intervention cluster) or SMC drugs only (control cluster). Given that 4‐aminoquinoline drugs are reported to have antagonistic pharmacological interactions with PZQ [23], the SMC partner drugs, AQ (a 4‐aminoquinoline derivative) and SP will not be administered with anthelminthic drugs (ALB and PZQ) on the same day in this study. Therefore, eligible children randomised into the intervention clusters will receive ALB and PZQ on Day 0 and those randomised into the control clusters will receive vitamin A and zinc supplement as control drugs on this day. On the following day, which corresponding to the start (Day 1) of the first SMC cycle, the children in the control and intervention clusters will receive SPAQ according to the WHO and Ghana SMC implementation guidelines. This will be followed on the second and third day of the SMC cycle with all study children in the two groups receiving AQ, in line with the SMC guidelines [5]. The study will administer AQ on Days 2 and 3 to the children in the presence of their parents/caregivers. Trained field workers will visit all enrolled children daily, irrespective of the study arms, at home starting from the evening of Day 0 till 3 days after completion of the first cycle of SMC course, using a purpose‐designed electronic diary card, to collect adverse drug reactions and adverse events such as vomiting, skin rash, body weakness, etc. Trained research assistants will visit each child 1 month after each round of SMC cycle to check that there are no severe reactions to the previous treatment and to give the next round of treatment (Table 1).

**TABLE 1 tmi14062-tbl-0001:** Schematic diagram of the study procedures for the effectiveness study.

SMC cycle	1					2, 3 and 4	End of malaria season (i.e., 1 month after completion of the last SMC cycle)
Timelines (days)	Pre‐intervention survey	Day 0	Day 1	Days 2 and 3	Days 4–6		Post‐intervention survey

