Study procedures						Passive surveillance involving collection of cases of breakthrough clinical malaria during the monthly cycle of SMC drugs administration according to WHO guidelines till the end of the malaria season	
Informed consent ± assent	X						
Enrolment and questionnaire administration to parents/caregivers	X						
Distribution of collecting bottles for stool sample a day preceding sample collection day.	X						
Sample collection (finger‐prick blood, urine, stool samples)	X	X					
Randomisation and intervention		X					
Intervention villages: SMC + anthelminthics		ALB + PZQ	AQ + SP	AQ			
Control villages: SMC + placebo		Vit A + Zn	AQ + SP	AQ			
Safety assessments (active surveillance)		X	X	X	X		
Post‐intervention survey							X
Sample collection: Finger‐prick							X
Sample collection: stool							X
Sample collection: urine							X

Abbreviations: ALB, albendazole; AQ, amodiaquine; PZQ, praziquantel; SMC, seasonal malaria chemoprevention; SP, sulphadoxine‐pyrimethamine Vit A, vitamin A; Zn, zinc.

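### The sampling section randomises schools and reads as enrolling children after allocation, while the rest of the article randomises communities and enrols before Day 0

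*Protocol article*

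**What the plan says.** All places are in the protocol article.

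**Unit of randomisation**
- Sampling for the intervention stage: "Ten schools within Pru East communities will be randomised to the intervention arm and another 10 schools will be randomised to the control arm".
- Study design: "The children will be enrolled at community levels and the communities will be assigned into two equal clusters".
- Intervention stage: "the communities will be randomised at community level into two clusters at 1:1 ratio", on Day 0.
- Sample size determination works with 10 communities per arm and 60 children per community.
- Study design also says that "the study communities will be separated from each other by at least 5 km". No distance is given for schools.

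**Selection and timing of enrolment**
- Sampling for the intervention stage: "a minimum of 60 children who satisfy all eligibility criteria will be enrolled sequentially in each of the 10 schools randomised". To find these children the team will take a census of the communities, and "we will use a sampling frame for random sampling from the census list" to fill each arm. It adds: "We will keep a reserve list of potentially eligible children in case of any refusals from the sampling list".
- Table 1: the row "Enrolment and questionnaire administration to parents/caregivers" is marked only under the pre-intervention survey, as is consent. Randomisation is marked on Day 0, when the first study products are given.
- Sampling for the pre-intervention stage: 15 children per school, given as an example.

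**Events on or after Day 0 that bear on enrolment**
- Eligibility criteria exclude a child who is acutely ill when the drugs are given.
- Box 1 says that a child who vomits the medication a second time is not enrolled.
- The Statistical analysis plan section specifies intention-to-treat (ITT).

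**The concern.** In a cluster randomised trial, randomisation protects the comparison of children only if they are identified and consented without knowledge of their cluster's allocation. Otherwise the clusters are randomised but the children in them may be selected differently by arm. ITT does not correct this, because it keeps whoever was enrolled.

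The sampling section describes enrolment into schools already called randomised, and into arms, with replacement of refusals. Table 1 gives the opposite order. A field team holding this text could follow either.

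The choice of unit matters for a second reason. The 5 km separation is the stated protection against contamination, and it is defined between communities. If two randomised schools lay in one community, it would not apply between them.

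**Working it through.** **1. The plan's own figure.** Inputs from Sample size determination: difference 0.5 g/dL, SD 1.5 g/dL, intra-class correlation 0.05, 60 children per community, 10 communities per arm, 5% level. The Statistical analysis plan section makes tests two-sided.
- Design effect = 1 + (60 − 1) × 0.05 = 3.95.
- Effective number per arm = 600 / 3.95 = 151.9.
- Standard error of the difference = 1.5 × √(2 / 151.9) = 0.172 g/dL.
- Power = 82.8% by the normal approximation, and 78.4% by the noncentral t on 20 − 2 = 18 degrees of freedom.
- Total = 2 × 10 × 60 = 1200.

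The stated 80% lies between the two results. The sample size is not in error on this point, and naming one unit changes no figure.

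**2. Can the pre-intervention survey be the enrolment step?** Assume it covers the 20 trial schools at the example of 15 each.
- 15 × 20 = 300 children.
- Shortfall = 1200 − 300 = 900.
- Schools needed at 15 each = 1200 / 15 = 80.

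So Table 1's enrolment mark under that survey cannot cover the whole cohort unless a larger round of consent is held before Day 0, and the article does not describe one.

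**3. Unit, side by side.**

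| Section | Unit | Number |
|---|---|---|
| Study design | community | two equal groups |
| Sample size determination | community | 10 per arm × 60 |
| Sampling for the intervention stage | school | 10 per arm × 60 |
| Intervention stage | community | 1:1 |

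The two counts agree if there is one school per community. No section says so. The wording on the pre-intervention survey would allow more than one school in a selected community.

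**4. Order, side by side.** Sampling section: schools randomised, then children enrolled, refusals replaced. Table 1: consent and enrolment, then randomisation on Day 0. No section says when the reserve list may be used, or in what order its names are taken.

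**5. Purely illustrative size.** The documents give no figures for this. If a share *f* of one arm were replaced by children whose Hb differs by *g*, mean Hb in that arm would shift by *f* × *g*. With *f* from 10% to 30% and *g* from 0.25 to 1.0 g/dL, both assumed, the shift is 0.025 to 0.30 g/dL. With a standard error of 0.172 and 18 degrees of freedom, a bias of 0.05 or 0.10 g/dL in the analysed difference would raise the two-sided type I error from 5% to about 5.9% or 8.5%. The primary endpoint is change in Hb, and a difference in baseline level does not carry over one-for-one to a change. The conclusion does not rest on this calculation.

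**The case against.** The best defence is that the article, read as a whole, describes a sound sequence loosely.

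- **Sequential against random.** The sampling section goes straight on to explain that the children are found by census and random draw. Working down a random list until 60 eligible children have consented is both sequential and random. This stands: a reader might infer a contradiction, but the text needs only clarification.
- **Enrolment after allocation.** The sampling section gives no dates, and its references to randomised schools and to arms may merely identify the clusters. Table 1, which does fix timing, puts enrolment first. This stands in part. It rules out saying that recruitment will follow allocation. It does not settle the matter, because the survey to which Table 1 attaches enrolment is too small at its stated example.
- **Reserve list.** It is tied to refusals, and nothing says that it is used after allocation. Used earlier, in a pre-set random order, it would be harmless. This stands.
- **Knowledge of arm.** A reader might infer that staff and caregivers know the arm when consenting. The article does not say so. Box 1 describes products that differ in form, given in front of caregivers, so knowledge of arm once dosing starts is a reasonable inference. The control products are meant to keep adverse-event reporting objective, and only laboratory staff are said to be masked.
- **Fewer than 20 independent units.** This would follow only if randomised schools shared a community. The matching counts suggest that they do not, so it is hypothetical.
- **Detectability.** Infection status is measured before treatment and summarised by arm, so gross imbalance could be seen. That helps detection but does not prevent selection on unmeasured characteristics.

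**Conclusion.** Two conflicts stand in the text and should be resolved: school against community as the unit of randomisation, and enrolment after against before allocation. On the assumption of 20 surveyed schools at 15 children each, the article leaves the timing of consent open for about 900 of the 1200 children.

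If the sampling section is followed, selection could differ by arm, and ITT would not remove that. This is conditional. The documents do not support a claim that recruitment bias will occur, that the 5 km separation fails, or that the bias has any particular size in g/dL. Sample size and power stand as stated.

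**What to change.** 1. In the sampling section, name the community as the unit of randomisation and state how schools map to communities.
2. State that the census, the random draw of at least 60 children per community, replacement from the reserve list in a pre-set random order, and consent are all completed, and the list closed, before the Day 0 allocation is revealed.
3. Say that *sequentially* means working down that random list.
4. Reconcile both sampling sections, the Intervention stage text and Table 1 with the exclusion for acute illness at drug administration in Eligibility criteria, the non-enrolment wording after vomiting in Box 1, and the ITT statement. Children on the closed list should stay in the ITT population whatever happens on or after Day 0. This concerns who is analysed and proposes no change to clinical management.

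The number of children stays at 1200 and the power is unchanged. Most of this is wording. The real cost is scheduling: consent for the full sample must be finished before Day 0, which is four times the 300 children that the survey example would yield in 20 schools.

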### Eligibility criteria

Inclusion criteria will include male and female children aged 5–10 years whose parents/caregivers are willing to provide written informed consent and a positive assent by children aged ≥7 years (in line with legal regulations in Ghana); willingness to provide finger‐prick blood samples, urine and stool samples; residency in the study area for at least the past 6 months and willingness to be available in the study area for about 6 months of follow‐up after enrolment. Exclusion criteria will include an acutely ill child at the time of the drug administration; a child whose parent/caregiver declines to provide consent; a known human immunodeficiency virus (HIV) positive child receiving co‐trimoxazole prophylaxis; a child who has received a dose of either SP or AQ in the previous 28 days; a child who has received ALB or PZQ during the previous 6 months; and a child with a known allergy to any of the study drugs.

